## Abstract

**Introduction:**

The quantity and quality of surgical training in the UK has been negatively affected by reduced working hours and National Health Service (NHS) financial pressures. Traditionally surgical training has occurred by the master-apprentice model involving a process of graduated responsibility, but a modern alternative is to use simulation for the early stages of training. It is not known if simulation training for junior trainees can safeguard patients and improve clinical outcomes. This paper details the protocol for a multicentre randomised controlled educational trial of a cadaveric simulation training intervention versus standard training for junior postgraduate orthopaedic surgeons-in-training. This is the first study to assess the effect of cadaveric simulation training for open surgery on patient outcome. The feasibility of delivering cadaveric training, use of radiographic and clinical outcome measures to assess impact and the challenges of upscaling provision will be explored.

**Methods and analysis:**

We will recruit postgraduate orthopaedic surgeons-in-training in the first 3 years (of 8) of the specialist training programme. Participants will be block randomised and allocated to either cadaveric simulation or standard ‘on-the-job’ training, learning three common orthopaedic procedures, each of which is a substudy within the trial. The procedures are (1) dynamic hip screw, (2) hemiarthroplasty and (3) ankle fracture fixation. These procedures have been selected as they are very common procedures which are routinely performed by junior surgeons-in-training. A pragmatic approach to sample size is taken in lieu of a formal power calculation as this is novel exploratory work with no a priori estimate of effect size to reference. The primary outcome measure is the technical success of the surgery performed on patients by the participating surgeons-in-training during the follow-up period for the three substudy procedures, as measured by the implant position on the postoperative radiograph. The secondary outcome measures are procedure time, postoperative complication rate and patient health state at 4 months postoperation (EQ-5D—substudies 1 and 2 only).

**Ethics, registration and dissemination:**

National research ethics approval was granted for this study by the NHS Research Authority South Birmingham Research Ethics Committee (15/WM/0464). Confidentiality Advisory Group approval was granted for accessing radiographic and outcome data without patient consent on 27 February 2017 (16/CAG/0125). The results of this trial will be submitted to a peer-reviewed journal and will inform educational and clinical practice.

**Trial registration number:**

ISRCTN20431944

Strengths and limitations of this studyThis is the first randomised controlled trial assessing the impact of cadaveric simulation training on clinical outcomes.Patient-centred outcome measures are used to measure an educational intervention for surgeons.Multicentre study to maximise external validity of the results.The training dose is small as cadaveric training is expense to deliver.Pragmatic approach to sample size which is limited by the capacity of the surgical training centre.

## Introduction

It is imperative that surgeons are trained to a high standard, so they can perform safe and effective operations for patients. The quality and quantity of surgical training in the UK is currently under threat from a ‘perfect storm’ of factors.^1^ These include reduced working hours,^2 3^ shift-based working patterns^4^ with the loss of the traditional surgical firm and a move to expedite training and shorten specialist programmes.^5 6^ This is set within a climate of unprecedented financial austerity in the NHS and ever-increasing service pressures.

Simulation offers a solution to some of these challenges by moving the early part of the surgical learning curve away from patients into a controlled environment,^7^ where skills may be more rapidly acquired as compared with the clinical environment. Simulation is also potentially a very efficient way of training, as large numbers of trainees can be trained simultaneously, at an intensity not feasible in the clinical environment due to competing service demands.

Cadaveric simulation—training using deceased, preserved or fresh human bodies—is a particularly promising modality for training. Fresh-frozen cadavers retain many of the soft tissue handling characteristics seen in live patients, and in combination with presenting the correct anatomy, particularly complex neurovascular relationships, may offer a more realistic simulated operation than would be possible on a plastic model or virtual reality simulator.^8 9^ Cadaveric material does not bleed^10^ and hence may be less useful for simulating procedures where haemorrhage control is an important feature.

The operating theatre environment can be simulated, including (but not limited to) surgical dress, draping, instrumentation and multidisciplinary team. This ‘whole dress rehearsal’ for surgery may enhance development of non-technical skills in addition to the technical operative surgical skills.^11^

There are several challenges in delivering cadaveric simulation training. It is expensive to provide,^9^ particularly when cadaveric material has to be purchased under license, where there is not a local body donation programme. It requires considerable infrastructure to deliver, including specialist wet laboratory facilities with the appropriately trained staff. These challenges become particularly pressing when provision of cadaveric training on a large scale is considered, and are an important driver in the development of high-quality evidence of educational impact. This evidence is necessary before considerable financial investment can be recommended in providing cadaveric simulation training on a larger scale.

There is abundant low-quality evidence showing cadaveric simulation may induce short-term skill improvement as measured by subjective and behavioural metrics, but there is a lack of high-quality, quantitative evidence that skills learnt in cadaveric simulation can transfer to the workplace, leading to improved outcomes for patients.^8^

Our trial attempts to address this evidence deficit, and is both topical and timely.

## Good clinical practice

This trial will be undertaken in compliance with Good Practice Guidelines, complying with the Declaration of Helsinki and UK Legislation. Warwick standard operating procedures (SOPs) will be followed.

## Consolidated standards of reporting trials

The results of the trial will be reported in line with the Consolidated Standards of Reporting Trials (CONSORT) statement.^12^ This protocol has been written according to the Standard Protocol Items: Recommendations for Interventional Trials reporting guidelines.^13^

## Aim

The aim is to determine which of the two surgical training strategies for junior orthopaedic surgeons-in-training lead to the best patient outcomes for three common procedures.

## Objectives

To assess the impact of a cadaveric simulation training intervention on the patient outcome of operations performed by junior orthopaedic surgeons-in-training.To define the early learning curve of dynamic hip screw (DHS), hemiarthroplasty and ankle fracture fixation.To explore the feasibility of using postoperative X-rays to assess technical skill.

## Methods and analysis

### Study design

This is a UK multicentre, two-arm, group parallel randomised controlled educational trial.

### Sample size

This trial is the first attempt to objectively measure transfer of open operative skills from cadaveric simulation into the workplace using patient-based outcome measures. There is no available estimate of effect size to reference against a priori in determining sample size, therefore a pragmatic approach to sample size will be taken in lieu of a formal power calculation. The surgical training centre can accommodate 16 delegates at one time and financial resources permitted one iteration of the cadaveric training course. Our maximum sample size is therefore 16 participants in each arm of the study.

## Outcome measures

### Radiographic outcomes

The radiographs will be obtained electronically from hospital servers and the implant position measured manually using computer software. The operations will be identified retrospectively by access to the participating surgeons’ electronic logbooks. The measurements vary by operation type and are defined as follows.

#### Substudy 1: DHS

Primary outcomeTip–apex distance (mm).Secondary outcomes (in order of importance)Lag screw position in the femoral head (defined by Cleveland Zones).Plate flush to lateral femoral cortex (binary Y/N).Eight cortex hold for plate screws (binary Y/N).

#### Substudy 2: hemiarthroplasty

Primary outcomeLeg length discrepancy (mm).Secondary outcomes (in order of importance).Femoral stem alignment (degrees off neutral).Cement mantle quality (Barrack grade score).Femoral offset change relative to native hip (mm).

#### Substudy 3: ankle fracture fixation

Primary outcomeMedial clear space (mm).Secondary outcomesLateral malleolar displacement (mm).Tibiofibular clear space (mm).Talocrural angle (degrees).Medial malleolar displacement (mm).

### Clinical outcomes

The clinical outcome measures for substudies 1–3 are as follows:

Procedure timeDefined as knife-to-skin/surgical start time to wound closure/surgical stop time. These will be obtained from hospital theatre management systems. Procedure time has been chosen as an outcome measure as there is evidence in the literature that procedure time is inversely related to experience, and so can be used as a surrogate measure of technical proficiency.^14^Intraoperative radiation dose to patientDefined as time under fluoroscopy (seconds) and radiation dose (mGym^2^). There is evidence that with increasing experience and skill, surgeons use less intraoperative X-rays to adjust the position of the fracture and implant.^14^ Hemiarthroplasty does not require fluoroscopy so this will not be used as an outcome measure for substudy 2.Postoperative complication rateThe complications of interest are the acute postoperative complications during the inpatient admission. These will be subcategorised as acute medical complications (hospital-acquired pneumonia, renal complications, cardiac complications, Deep Vein Thrombsis (DVT)/Pulmonary Embolism (PE) and surgical complications (wound infection, wound dehiscence, metalwork failure, deep infection).Health state at 4 months postoperation (EQ-5D).Health state at 4 months postoperation will be measured using EQ-5D, which is a standardised instrument measuring generic health status, which has been widely validated in clinical trials. These data are being collected separately as part of the WHiTE comprehensive cohort study of patients with hip fracture (ISRCTN63982700) and reported elsewhere.^15^ EQ-5D will be used for substudies 1 and 2 only as these involve hip fractures.

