#### Patients whose operations are assessed

Patients who undergo an operation by a surgeon who is participating in the study will not be separately consented to allow access to radiographs to assess their implant position or clinical outcome data. Permission to access this information for the purposes of this study without patient consent has been granted from the confidentiality advisory group (16/CAG/0125). It is recognised that seeking consent from a group of primarily elderly, frail patients to assess low risk, routine clinical data in a secure manner for a trial they are not directly participating in would be unduly burdensome for the patients. All patient data will be fully anonymised and handled securely in line with university data regulations.

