### Study setting

The study participants will be on training rotations within the regional hospitals of the West Midlands during the study follow-up. The hospitals where trainees have been working, and performing operations, during the study follow-up will be identified from the participants electronic surgical logbook records.

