### Data collection plan

Data on the numbers of procedures performed by the participating surgeons at baseline will be collected. The operations performed by the participants during study follow-up will be identified by the surgeons’ electronic logbook. Only procedures coded as ‘S-TS: supervised-trainer scrubbed’ or ‘S-TU: supervised trainer unscrubbed’ will be included in the analysis. This is to ensure that only procedures where the trainee has performed the key parts (S-TS) or the entire procedure (S-TU) are included. If further information on supervisor input/takeover is required this can be obtained by accessing the corresponding procedure based assessment (PBA) record for the operation. PBAs are routinely collected as part of training.

Procedure data will be extracted and anonymised to study identifier by the electronic logbook data team, before being sent to the trial team. The data will include operation type, date, hospital, hospital ID, patient age, American Society of Anaesthesiologists Grade and supervision code. The radiographs and clinical outcome data relating to these procedures will then be obtained from the study sites via liaison with the respective Research & Development Departments. Data will be entered into a secure trial database on a professionally encrypted trial-specific computer, fully anonymised with only study identifiers. Once data collection is complete, and prior to analysis, range checks for data values will be undertaken, and data will be double checked on entry to the statistical software package. The project supervisors will act as the data monitoring committee. No interim analysis will be undertaken. The trial team and statistician will have access to the final trial dataset.

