### Statistical analysis plan

Baseline data including completed months of training and number of prior procedures performed will be summarised and compared between the two arms of the study. A CONSORT chart showing the flow of participants through the study will be produced. The three taught procedures (substudies 1–3) will be analysed and reported individually.

The main analysis will investigate and report differences between the two groups with respect to the implant positions (as measured from radiographs), the procedure times, the intraoperative radiation dose to the patient, and patient outcomes, as measured by postoperative complications and health state at 4 months postoperation (hip fractures only).

Statistical tests will be two-sided and considered to demonstrate a significant difference when p<0.05. Temporal trends by group for implant position, procedure time and radiation dose will be presented. Linear mixed-effects models will be fitted to allow for within-surgeon correlation between repeated observations (surgeon clustering as a random effect), and to adjust for important covariates such as patient condition, age and surgeon experience. These will be summarised by plotting individual learning curves, and then modelled to estimate the overall learning curves for the two arms of the study.

Descriptive statistical analyses of between-group comparisons will be presented for complication rate and health state, with temporal analysis of the latter being reported if appropriate and feasible. The statistical analysis will be supervised and checked by a senior medical statistician at Warwick University.

In the event of missing data, statistician advice will be sought on multiple imputation.

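### Four-month EQ-5D comes only from an outside cohort of unstated coverage and is compared between arms only descriptively, so chance differences in coverage and case mix can pass for a training effect

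*Protocol article*

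**What the plan says.** All places are in the protocol article.

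- **Rank.** The abstract lists health state among the secondary outcomes: "The secondary outcome measures are procedure time, postoperative complication rate and patient health state at 4 months postoperation".
- **Source.** Under Clinical outcomes, the 4-month EQ-5D is taken from another study: "These data are being collected separately as part of the WHiTE comprehensive cohort study of patients with hip fracture".
- **Scope.** The only limit stated there is by diagnosis: "EQ-5D will be used for substudies 1 and 2 only as these involve hip fractures". Cohort membership is not mentioned as a condition.
- **How operations enter.** Data collection plan: "The operations performed by the participants during study follow-up will be identified by the surgeons’ electronic logbook". Two supervision codes qualify an operation, and neither depends on the cohort. Study setting: "The study participants will be on training rotations within the regional hospitals of the West Midlands during the study follow-up". Whether those hospitals take part in the cohort study is not said.
- **Analysis.** The Statistical analysis plan section describes mixed-effects models with a surgeon random effect and adjustment for patient condition, age and surgeon experience. Complications and health state are instead assigned descriptive between-group comparisons, with a temporal analysis of health state only if that proves suitable and possible.
- **Missing data.** One general sentence: "In the event of missing data, statistician advice will be sought on multiple imputation".
- **Randomisation.** Surgeons are randomised in blocks of 4, at most 16 per arm. No stratification by hospital is described.

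**The concern.** The logbooks decide which hip operations count. A different study decides which of them have an EQ-5D value. If the two sets differ, the comparison is made on a subset whose make-up the trial does not control, and randomising at most 32 surgeons does not guarantee that this subset is alike in both arms.

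Trainees' hospitals vary, and so may the cohort's reach at each hospital and among frailer patients. A descriptive, unadjusted comparison carries any resulting imbalance straight into the arm difference. What is at stake is the trial's only patient-reported outcome, in a trial whose stated aim is to find which training strategy gives patients the better result. A small spurious difference in health state could be read as an effect of cadaveric training, or could hide one.

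**Working it through.** **What can be reproduced.** The only relevant planned figure is 16 surgeons per arm. It is the training centre's capacity of 16 for one course, so at most 2 × 16 = 32 surgeons. The protocol gives no expected EQ-5D coverage, so coverage and EQ-5D gaps below are assumptions shown as ranges.

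**Step 1: bias when coverage differs between arms.** Let c be the share of hip operations with cohort data, and let the gap be mean EQ-5D of cohort members minus that of non-members. Assume that all operated patients have the same mean in both arms apart from any true effect, and that the gap and the true effect are the same in both arms and in both groups. From overall mean = member mean − (1 − c) × gap, it follows that member mean = overall mean + (1 − c) × gap. Hence

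bias in (intervention − control) = gap × (c control − c intervention).

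| Coverage, control v intervention | Gap 0.05 | Gap 0.10 | Gap 0.20 |
|---|---|---|---|
| 50% v 50% | 0 | 0 | 0 |
| 60% v 50% | 0.005 | 0.010 | 0.020 |
| 70% v 40% | 0.015 | 0.030 | 0.060 |

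**Step 2: how far coverage could differ by chance.** Suppose each surgeon works at one hospital that is either wholly in or wholly out of the cohort, surgeons are independent, and each does the same number of operations. Then SD of the coverage difference = √(2c(1 − c)/16).

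- c = 0.5: √(0.5/16) = 0.177; 95% range ±1.96 × 0.177 = ±0.35.
- c = 0.3 or 0.7: √(0.42/16) = 0.162; ±0.32.
- c = 0.9: √(0.18/16) = 0.106; ±0.21.

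This is a rough guide: rotation between hospitals would shrink these figures. Steps 1 and 2 should not be multiplied together. If coverage were purely all-or-none by hospital, the covered patients in both arms would come from the same set of hospitals. The cost would then be fewer contributing surgeons, and so more room for chance differences in case mix.

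**Step 3: case mix with equal overall coverage.** Assume half the patients are fit (mean 0.70) and half frail (mean 0.40). The covered mean is (c fit × 0.70 + c frail × 0.40)/(c fit + c frail).

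- 80%/40% in one arm: (0.56 + 0.16)/1.20 = 0.60. 60%/60% in the other: (0.42 + 0.24)/1.20 = 0.55. False difference 0.05, although overall coverage is 60% in both arms.
- 70%/50%: (0.49 + 0.20)/1.20 = 0.575, against 0.55. False difference 0.025.

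So a count of covered patients is not enough by itself; case mix has to be handled as well. With the same fit/frail pattern in both arms the false difference is zero.

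**The case against.** The strongest reply is that little here is stated wrongly. The article does not describe the cohort's hospitals, consent or response, so coverage might be nearly complete. Surgeons are randomised, so an imbalance in coverage would arise by chance and not by design. The comparison is secondary and labelled descriptive, and analysis sets and coverage tables are commonly left to a statistical analysis plan that is not shown.

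Much of this stands. The absence of an analysis-set definition or a coverage table would not be a finding on its own, and the bias figures are illustrations. What remains is the method the article does fix. It takes the outcome from outside the trial, sets the scope by diagnosis alone, and assigns health state an unadjusted descriptive comparison while adjusting its modelled outcomes for patient condition and age. Calling a comparison descriptive does not protect it from imbalance, and 32 surgeons are few enough for chance to matter.

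Four stronger readings should be resisted.

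- *Imputation of EQ-5D is planned.* It is not. The one sentence on missing data says that advice will be sought; it does not name EQ-5D or commit to imputing anything.
- *The patients with EQ-5D are self-selected.* The article does not say how patients join the cohort, nor what share is left out.
- *Every hip operation is meant to have a value.* The wording leans that way but does not say so, and only operations with the qualifying supervision codes count.
- *Anonymisation prevents linkage.* The article does say "All patient data will be fully anonymised and handled securely in line with university data regulations" and describes the database as "fully anonymised with only study identifiers". But the logbook extract carries a hospital ID as well as the hospital and is tied to a study identifier, and sites must match operations to patients to supply radiographs. The terms are loose; they do not show that linkage is impossible.

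**Conclusion.** The concern holds in a limited form. The EQ-5D comparison in substudies 1 and 2 depends on an outside cohort of unstated coverage, and the planned descriptive comparison leaves chance differences in coverage and case mix unadjusted.

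Bias in the arm difference needs coverage, the member/non-member gap or the mix of covered patients to differ between arms. If these are alike, and the training effect is the same inside and outside the cohort, the loss is in precision and generalisability only. The size is unknown. The assumed scenarios give about 0.005 to 0.06, resting on arm coverages of 60% v 50% to 70% v 40% and gaps of 0.05 to 0.20; none of these inputs is in the protocol. The primary radiographic outcomes are not touched. The change is worth making because it is cheap and improves on the stated method.

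**What to change.** - Restrict the EQ-5D comparison in substudies 1 and 2 to operations on patients in the cohort study, and say so.
- State that EQ-5D will not be imputed for patients who were never in the cohort. Non-enrolment differs from a missed 4-month response, and any advice on imputation should concern only the latter.
- Estimate the arm difference with the surgeon random effect already planned for other outcomes, adjusted for age and ASA grade. Both are already in the logbook extract. Add hospital, also extracted, as a sensitivity analysis.
- Report by arm the number of qualifying hip operations, the number on cohort patients and the number with a 4-month value.

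Adjustment removes only the imbalance that age and ASA grade explain, so the coverage counts remain necessary for interpretation.

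Cost: a few sentences, one short table, one more model per hip substudy and its sensitivity analysis, with no new extraction from the logbooks. The downside is a smaller stated EQ-5D sample.
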